### External validation of the DRPTVL-UK model

The DRPTVL-UK model will be used to obtain the predicted probability of the outcome over time for every participant within each of the three trusts. Predictive performance of the model will be assessed using measures of discrimination (Harrell’s C-statistic and time-dependent C-statistic), calibration (calibration slope, ratio of observed to expected probabilities, calibration plots at multiple time points up to 2 years) and net benefit using decision curves. Performance measures will be calculated within each hospital and then pooled on an appropriate scale using random effects meta-analysis to account for clustering by hospital.^26^

As another potential use of the model would be to determine appropriate follow-up intervals based on the individual’s risk, it will also be crucial to ensure that the model performs well for predictions at all time points up to 2 years to ensure risk predictions are accurate over time. Therefore, we will also evaluate calibration performance at multiple time points. In addition to this, we will look at the predictions over time (predicted survival curves) and compare these to the observed survival curves for risk groups and other meaningful groupings, for example, DR grade.

In addition to external validation of the model in the whole sample, we will also validate the model within the subgroups of R2/M1 patients to see how well it performs in each.

### Summarising baseline variables

Baseline variables will include predictors measured at referral or shortly before (see table 1 for full list of variables to be collected). Continuous variables will be described using means and SDs (prior to centring and standardisation), binary or categorical variables will be described using frequencies and proportions.

**Table 1 T1:** List of variables for data collection—predictors modified from,^21^ outcomes and competing risk variables

	Group	Required variables	Source, units
1	Ocular features*	Diabetic retinopathy grade	DESP/hospital notes/letter
2		Visual acuity score	Both eyes, log MAR, every visit with date till the outcome
3	Biochemical parameters	Glycated haemoglobin (HbA1c)	From biochemistry database (mmol/mol)
4		Estimated glomerular filtration rate (eGFR)	From biochemistry database, mL/min/1.73 m^2^
5		Total serum cholesterol	From biochemistry database, mmol/l
6	Physical examination	Systolic blood pressure	From nursing notes, mm Hg
7	Diabetes treatment	Statin	From General Practitioner (GP) letter/diabetology notes
8		Insulin	From GP letter/diabetology notes
9	NGT*	Pregnancy	During the preceding 2 years before referral
10		Early worsening	To be calculated at baseline (details in online supplemental appendices 2 and 3).
11		Frequent DNA/cancellations (total, two consecutive sets)	With dates (patient administration system)
12	Competing risk	Date of death if occurring before the treatment/ vision failure/date of discharge	Patient administration system, deidentify after
13	Outcome/follow-up	Date of treatment (first ever)/vision failure/ discharge/transfer/end of the study—end December 2021 (whichever happens first)	Patient notes
14	Demographics	Age, gender, ethnicity and deprivation score	Patient notes

*Among the predictors, ocular features (DR stage in each eye) and visual acuity will be recorded for both eyes at every visit along with the date of measurement. For analysis, the eye with the higher DR grade will be used (R3M1>R3>R2 M1>M1>R2). For other predictors in the model, values up to and including the first referral (baseline) appointment will be used, provided they occur in the 12 months prior to the referral appointment. The measurement closest to the referral (baseline) appointment will be used. Please also see online supplemental appendices 2 and 3 for details.

DESP, Diabetic Eye Screening Programme; DNA, did not attend; DR, diabetic retinopathy; NGT, Nominal Group Technique.

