The current length of follow-up intervals used within HES is based on the probability of disease progression from a study conducted in the late eighties^18^ and not based on the patient’s individual risk. We therefore aim to predict the progression of DR to treatment stage, to direct resources toward higher-risk patients so that they are followed up and treated before vision failure occurs. We propose that use of a validated risk prediction model will facilitate evidence-based decisions and thus reduce the chance of harm to higher-risk patients.

There are two recent systematic reviews of existing models for predicting the progression of DR among the DESP population.^15 19^ A review by this group of researchers found a total of 14 predictive model development studies of which 11 had been internally validated, 8 had been externally validated and only three without risk of bias.^15^ In a more recent review, there were 16 model development studies for an outcome of referable DR.^20^ Based on these two reviews, it was concluded that none of the existing models were intended for our target population (patients under care of HES/surveillance clinics) and none used the clinically important outcomes of interest (including contemporary treatment modalities and vision loss). Therefore, a prediction model that could be used to identify patients with a higher probability of requiring treatment or at high risk of loss of vision for HES was needed.

In brief, the DRPTVL-UK model was developed in anonymised, retrospective primary care data from IQVIA Medical Research Data (IMRD). From predictors identified in our systematic review,^15^ we selected a set of 19 clinically meaningful candidate predictors of DR progression using the Nominal Group Technique.^21^ A prediction model was then developed considering 15 of the 19 candidate predictors for inclusion based on availability in the dataset.^22^ After variable selection, the final model included seven predictors, namely (1) retinopathy stage, (2) glycated haemoglobin (HbA1c), (3) estimated glomerular filtration rate (eGFR), (4) total serum cholesterol, (5) systolic blood pressure and drug use of (6) insulin or (7) statins. The DRPTVL-UK model demonstrated moderately good discriminative performance (C-statistic=0.74) and very little optimism (0.004) in the internal validation due to the large sample size (13 691 patients).

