### Study population

The cohort will include type 1 and type 2 patients with diabetes, aged 12 years and over (as patients enter the screening programme from age 12), referred into HES or surveillance clinics with referable DR from DESP for close monitoring and treatment. Data will be collected from three NHS trusts for all patients within the catchment areas of Sandwell and Birmingham, Sunderland or Sussex NHS trusts. Records will be extracted for patients first entering the services between 1 January 2013 and 31 December 2016, with follow-up information extracted up to 31 December 2021. The Birmingham trust cares for an ethnically and socioeconomically diverse range of communities and was chosen to ensure equality, diversity and inclusion. The Sussex trust provides secondary care to a less diverse population and Sunderland is a primarily Caucasian population.

Patients with the specific outcome of retinopathy treatment or vision loss at referral or those referred for reasons other than retinopathy will be excluded. Patients objecting to their information being used (through a local or national opt out scheme) will also be excluded. Data flow and management stages are given in figure 2.

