### Data extraction

A data extraction sheet has been prepared using Microsoft Excel and will be piloted prior to use within each trust. Data will be extracted for all predictors at baseline (first HES appointment after referral) and visual acuity level will be collected at each follow-up appointment. Data will continue to be extracted until an outcome of interest occurs, death, lost to follow-up or the end of the study period (31 December 2021).

Personal information such as date of birth (for age calculation), date of diabetes diagnosis and date of death (for censoring or competing risks analysis) will be extracted. However, all the personal identifiable information will be removed after age, diabetes duration and follow-up durations have been calculated.

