### Outcomes

The primary outcome for this study is time to first treatment for DR or vision loss. Time will be calculated from referral to HES (baseline is first appointment) until the date of first treatment or vision loss. Time to death will also be recorded and treated as a competing risk if necessary.

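### Table 1 ends follow-up at discharge or transfer while the Data extraction text does not; outcomes after discharge may go uncollected and observed 2-year risk, O/E and calibration plots may be biased

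*Protocol article*

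**What the plan says.** Two places in the protocol article say when follow-up stops.

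- Table 1 (under Summarising baseline variables), row 13: "Date of treatment (first ever)/vision failure/ discharge/transfer/end of the study—end December 2021 (whichever happens first". Row 12, on death as a competing risk, reads "Date of death if occurring before the treatment/ vision failure/date of discharge", which appears to limit recorded deaths to those before discharge.
- Data extraction: "Data will continue to be extracted until an outcome of interest occurs, death, lost to follow-up or the end of the study period". Discharge and transfer are not named.

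On analysis, the Outcomes section says only "Time to death will also be recorded and treated as a competing risk if necessary". Nothing says how discharge enters the analysis, how often it occurs or why. Design and data sources lets trusts fill gaps in hospital records from surveillance clinics and the reverse, but describes no tracing after discharge.

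The cohort is "patients first entering the services between 1 January 2013 and 31 December 2016, with follow-up information extracted up to 31 December 2021". Performance is judged by "calibration (calibration slope, ratio of observed to expected probabilities, calibration plots at multiple time points up to 2 years" and by "discrimination (Harrell’s C-statistic and time-dependent C-statistic", together with net benefit.

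**The concern.** Discharge from a monitoring service is unlikely to be unrelated to prognosis. The Introduction says that 50%–78% of referrals do not yet need treatment. Some of these patients may be released because their disease is stable, on findings made after baseline that the seven baseline predictors do not capture. If they leave the risk set and are handled as ordinary censoring, the patients who remain are at higher risk, and the Kaplan–Meier estimate of observed risk is too high.

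A well-calibrated model could then appear to under-predict. Model recalibration and updating allows the baseline survival function to be updated if necessary, so the artefact could prompt an upward recalibration that is not needed. Performance is calculated by hospital and then pooled by random effects, so different discharge practice could pass for heterogeneity in the model.

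The data-collection side matters most. Under Data extraction and Ethics and dissemination, identifiers are removed once ages and follow-up durations are calculated, only anonymised data go to the university, and identifiable data are deleted at study end. No later analysis plan can recover events that were never extracted.

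**Working it through.** **1. The two rules side by side.** Take a patient discharged at 9 months and first treated at 18 months. Under Table 1, follow-up stops at 9 months with no event. Under the Data extraction list, unless discharge is counted as loss to follow-up, the patient has an event at 18 months. Extractors at three trusts could follow either rule.

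**2. Censoring inside the horizon.** The last entry date is 31 December 2016 and follow-up ends on 31 December 2021, so everyone has at least 5 years of potential follow-up. Nobody is administratively censored before 2 years.

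**3. Anchor from the plan.** The article has no discharge figure to reproduce. Its Sample size figures do reproduce: 3 × 200 × 4 = 2400 and 0.15 × 2400 = 360. Its event rate of 0.05 per year gives a 2-year risk of 1 − exp(−0.05 × 2) = 9.5%, so about 10% is a fair working value.

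**4. Two-group calculation (group sizes, risks and discharge rates are assumptions).** Shares p: 60% stable with 2-year risk 3%, and 40% progressing with 20.5%. True risk = 0.6 × 0.03 + 0.4 × 0.205 = 10.0%.

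- Event hazards λ = −ln(1 − risk)/2 = 0.0152 and 0.1147 per year.
- Discharge hazards γ = −ln(1 − proportion discharged)/2.
- Hazard among those still followed: h(t) = Σ pλ exp(−(λ+γ)t) / Σ p exp(−(λ+γ)t).
- Kaplan–Meier risk = 1 − exp(−H), where H is the integral of h from 0 to 2.
- If discharged patients are instead counted as event-free and no later event is found: Σ p [λ/(λ+γ)] [1 − exp(−2(λ+γ))].

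O/E below is relative to the true risk, so 1.00 is correct.

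| Discharged by 2 years: stable / progressing (overall) | H | Kaplan–Meier risk | O/E | Event-free rule | O/E |
|---|---|---|---|---|---|
| 30% / 5% (20%) | 0.1126 | 10.6% | 1.065 | 9.5% | 0.95 |
| 50% / 10% (34%) | 0.1195 | 11.3% | 1.126 | 9.1% | 0.91 |
| 70% / 10% (46%) | 0.1321 | 12.4% | 1.238 | 8.8% | 0.88 |

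A simulation of 400,000 patients with the same inputs gave Kaplan–Meier risks of 10.7%, 11.2% and 12.4%.

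**5. A different set-up.** This simulated 100,000 patients with a 2-year risk of about 9.5% and a C of about 0.745 under full follow-up (the article reports "The DRPTVL-UK model demonstrated moderately good discriminative performance (C-statistic=0.74" at development). Assumed dependence of the log-hazard of discharge: −0.7 per SD of the linear predictor and −1.0 per unit of an unmeasured factor with SD 0.7, with signs reversed when high-risk patients leave. Slope is given relative to full follow-up.

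| Discharge depends on | O/E at 20% / 40% / 60% discharged | Slope ratio | C |
|---|---|---|---|
| Nothing | 1.00–1.01 throughout | 1.00–1.01 | 0.745–0.755 |
| Low model risk | 1.05 / 1.12–1.13 / 1.23–1.24 | 0.99–1.01 | 0.73–0.75 |
| Low unmeasured risk | 1.035 / 1.089 / 1.157 | 1.00 | 0.744–0.748 |
| Both | 1.075 / 1.181 / 1.342 | 0.98 / 0.96 / 0.94 | 0.736 / 0.730 / 0.724 |
| High risk leaves | 0.87–0.91 / 0.74–0.84 / 0.59–0.73 | 0.89–1.02 | 0.717–0.753 |

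O/E moves materially. With low-risk discharge, slope changes by at most about 6% and C by about 0.02. Larger shifts (slope ratio 0.889, C 0.717) appear only when 60% are discharged and high-risk patients leave.

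**The case against.** A reader might infer that the plan treats discharge as ordinary censoring and will therefore overstate risk and distort calibration and C alike. The article does not support that.

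- **Handling is not stated.** Even the treatment of death is left open, and censoring rules commonly sit in an analysis plan that is not shown. This stands. It does not answer the collection point, because no analysis plan can use events that were not extracted.
- **Direction is not stated.** No reasons for discharge are given. Preproliferative patients are described as under regular review until progression, which does not suggest frequent early discharge of that group. Table 1 also collects non-attendance, and discharge after non-attendance could remove higher-risk patients. This stands, so the sign is conditional.
- **Discharge is not defined.** The cohort spans hospital and surveillance clinics, and each can fill the other's gaps, so a move between them need not end follow-up. This stands in part: return to routine screening is not covered.
- **The lists may not conflict.** Loss to follow-up could be read to include discharge and transfer. That reading is possible, but Table 1 would then still be the operative rule, and later events would still go uncollected.
- **Slope and C are little affected.** Slope, and curves within risk groups, need independence only given the predictors or the group. This stands.
- **Sampling error is comparable.** At 10% risk, 2400 patients give 240 events, and 1.96/√240 is about 13%. Per trust, 80 events give about 22%. Only the largest two-group scenario clearly exceeds the pooled margin. This is fair on size, but sampling error is shown in the confidence interval and this bias is not.

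**Conclusion.** The point holds in a limited form. Table 1 and Data extraction differ on whether follow-up runs past discharge or transfer, and the choice becomes irreversible once identifiers are removed. Since no administrative censoring occurs before 5 years, the handling of discharge could materially affect observed 2-year risk.

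The size is conditional. If discharge selects low-risk patients and is treated as ordinary censoring, observed risk, O/E and calibration plots are biased upward by about 6% to 24% in the two-group scenarios, and by about 4% to 34% across the wider simulation. If higher-risk patients leave, the bias is downward. Discharge rates, reasons, strength of dependence and method of analysis are all assumptions here. Effects on slope and C are small in comparison, and the article does not establish that the validation will be biased in either direction. This is worth correcting, but it does not invalidate the design.

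**What to change.** 1. Drop discharge as an end of extraction in Table 1, rows 12 and 13, in line with Data extraction, and say what discharge means (hospital clinic, surveillance clinic or both).
2. Record the date and reason of every discharge and transfer.
3. Before identifiers are removed, search trust and surveillance-clinic records for re-referral, first treatment, vision loss or death to at least 24 months from baseline.
4. For patients still untraced, censor, and add a sensitivity analysis with inverse-probability-of-censoring weights for O/E, calibration plots and net benefit. The retinopathy grade and visual acuity recorded at each visit can inform the weights.
5. Report two further analyses as a sensitivity range: untraced patients event-free to 24 months, and plain Kaplan–Meier censoring. The event-free rule should not be primary. If no later events are captured it reverses the bias, with O/E of 0.95, 0.91 and 0.88 in the scenarios above. The two analyses bracket the truth when discharge selects low-risk patients, but need not do so if higher-risk patients leave.

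The cost is a modest extra look-up per discharged patient (the patient administration system is already a listed source for non-attendance and death) and one further analysis. Treatment dates come from patient notes, so those must be searched too. Some events treated elsewhere would still be missed.

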### Model recalibration and updating

If necessary, we will recalibrate the model to the HES population (eg, by updating the baseline survival function or recalibrating the linear predictor).^27^ In addition, we will investigate whether updating the model to include additional predictors that were not available in the development dataset improves the predictive performance. Visual acuity, early worsening, pregnancy and frequent ‘did not attend’, were identified as candidate predictors based on expert opinion and evidence evaluation.^21^ To update the model with additional predictors, flexible parametric models (Royston-Parmar models) will be fitted using a multivariable fractional polynomial approach to consider non-linear functions for continuous variables while using backward elimination for the additional predictors considered.^28^ We will use a p>0.157 as a proxy for selection based on Akaike information criterion.^29^ All predictors from the original model will be forced to remain in the model regardless of statistical significance, therefore, only the four additional variables will be tested. The predictive performance of the updated model will be evaluated using internal–external cross-validation^30^ in which the model is developed using the data from two hospitals and externally validated in the third. This is then repeated a total of three times, each time reserving a different hospital for external validation. Predictive performance will be evaluated in each ‘external’ hospital using the same measures of discrimination and calibration as previously described and will be summarised across the hospitals using random-effects meta-analysis. Predictive performance of the updated model will be compared with the original model.

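### Pooled O/E from the three-hospital internal–external cross-validation tends to sit near 1 whatever the new predictors add, so it is not a fair basis for comparing the updated model with the fixed original

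*Protocol article*

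**What the plan says.** The section Model recalibration and updating plans an internal–external scheme. In each round, "the model is developed using the data from two hospitals and externally validated in the third". Three rounds are run, so every hospital is held out once. Each held-out hospital is assessed "using the same measures of discrimination and calibration as previously described", and the results "will be summarised across the hospitals using random-effects meta-analysis. Predictive performance of the updated model will be compared with the original model".

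The earlier measures are in External validation of the DRPTVL-UK model. Calibration there includes the "ratio of observed to expected probabilities", with hospital results "pooled on an appropriate scale using random effects meta-analysis to account for clustering by hospital".

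Objectives and outcome measures/endpoints makes it part of a primary objective to find out whether recalibration or additional predictors improve performance. The article does not say that pooled O/E decides the comparison. Nor does it say that the comparator is the original model recalibrated in the same folds.

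**The concern.** A model refitted on two hospitals takes its baseline risk from those two. When the folds rotate, every hospital serves once as the test set and twice as part of the reference. A hospital with high risk shows O/E above 1 when held out, and it pushes the other two below 1 when it is in training. Averaging over the folds largely cancels these deviations.

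The original model is fixed and was developed in other data, so its O/E values are free to average anywhere. Placing the two pooled values side by side compares a nearly constrained number with an unconstrained one. An update that carries no new predictor information can then look better calibrated overall while being worse in the individual hospitals. The random-effects standard error also assumes independent estimates, and these are not independent.

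**Working it through.** **Inputs.** From Sample size: about 200 referrals per trust per year for 4 years, so 200 x 4 = 800 per trust and 3 x 800 = 2400, as stated. The event rate of 0.05 per year gives a 2-year risk of 1 − exp(−0.05 x 2) = 9.5%. The article gives no figure for the cross-validated O/E. Hospital-specific risks, case mix and the log scale for pooling are assumptions here.

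**First-order algebra.** Let a_i be the log risk in hospital i, with equal sizes and the same case mix.

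log(O/E)_i ≈ a_i − (a_j + a_k)/2 = 1.5 (a_i − mean)

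The three values sum to about zero. Their pairwise correlation is about −0.5, as for any deviations from a mean of three.

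**Exact product.** With 2-year risks p1, p2, p3 in equal hospitals, the product of the three O/E values is 8·p1·p2·p3 / [(p1+p2)(p2+p3)(p1+p3)], which is at most 1.

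| 2-year risks | Held-out O/E | Product | Pooled (DerSimonian–Laird) |
|---|---|---|---|
| 8, 10, 12% | 0.73, 1.00, 1.33 | 0.97 | 0.996 |
| 15, 20, 25% | 0.67, 1.00, 1.43 | 0.95 | 0.99 |
| 6, 10, 14% | 0.50, 1.00, 1.75 | 0.875 | 0.96 |
| 5, 10, 20% | 0.33, 0.80, 2.67 | 0.71 | 0.90 |

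In the first row, an original model predicting 10% everywhere has O/E 0.80, 1.00, 1.20 and pools to 0.995. The update is further from 1 in both outer hospitals, yet the pooled values are alike. In the second row the same original pools to 1.97. With unequal sizes (300 to 1800 per hospital) the pooled value ranged from 0.75 to 1.18.

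**How often the update is truly better when the original is right on average.** Write m for the mean of the a_i around the original's prediction, and S = Σ(a_i − m)². The original's sum of squared log O/E is S + 3m²; the update's is 2.25 S. The update is better only if 3m² > 1.25 S. For normal a_i centred at zero this is P(F(1,2) > 2.5) = 1 − √(2.5/4.5) = 1 − 0.745 = 0.255.

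**Simulation, hospital shifts drawn at random** (3 x 800, 9.5% risk, same case mix, original right on average, update re-estimates the baseline only, 4000 runs per setting). For a between-hospital SD of the log hazard of 0 / 0.2 / 0.4 / 0.6:
- The update's pooled O/E is closer to 1 in 96 / 94 / 89 / 83% of runs.
- Its per-hospital root-mean-square log O/E is better in 25–26%, agreeing with the algebra.
- The true SD of pooled log O/E is 0.003–0.07, against an average stated SE of 0.09–0.43.
- With sizes 1200/800/400 and SD 0.2–0.6, the update is still closer in 81–86%.

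**Simulation, fixed shifts** (equal hospitals unless stated, 300 runs per setting). Mean |log O/E| per hospital is given as update v original.
- Original right on average, no shift: update closer on pooled O/E in 94%; 0.087 v 0.073.
- Original right on average, shifts ±0.2: closer in 91%; 0.209 v 0.145.
- Original right on average, shifts ±0.5: closer in 44%; 0.478 v 0.321. Adding case-mix differences gives 10%, and unequal sizes 6–23%.
- Original under-predicting by 0.3 on the log hazard (its pooled O/E about 1.3): closer in 100% at every shift. Per hospital the update is truly better with no shift (0.088 v 0.257) and at ±0.2 (0.204 v 0.265), but worse at ±0.5 (0.482 v 0.387).

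**The case against.** The best defence is that the plan does not rest on pooled O/E. Performance is evaluated in each held-out hospital before it is summarised, and calibration slope, calibration plots and C-statistics are compared as well. Random-effects meta-analysis also reports heterogeneity, which does carry the warning: median tau for the update against the original was 0.25 v 0.14 at SD 0.2 and 0.47 v 0.30 at SD 0.4. The standard error is too large, so it does not create false certainty. The model also moves from primary to secondary care, so average miscalibration is the very case for which updating exists. With the original off by 0.3 to 0.6 on the log hazard, the update's per-hospital calibration was truly better in 36–99% of runs.

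All of this stands, and it rules out three stronger readings that a reader might infer.
- That the planned analysis cannot show miscalibration: this applies at most to the pooled point estimate, because hospital-level O/E and tau do show it.
- That the comparison will favour the updated model: this is a tendency on one measure. It reverses in the fixed ±0.5 settings with a well-calibrated original, although those shifts sum to zero and so place the original's pooled O/E near 1 by assumption.
- That pooled O/E equals 1 by construction: the identity is first-order. It weakens with large hospital differences, unequal sizes or differing case mix, and Study population describes trusts with different populations.

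The objection does not remove the problem that pooled O/E is among the summaries to be compared. It also leaves no comparator that separates re-estimating the baseline from adding predictors.

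**Conclusion.** The concern holds in a limited form. With three hospitals of about 800 and modest risk differences, the updated model's pooled cross-validated O/E is weakly informative about calibration, its random-effects standard error is too large, and it is not a fair yardstick against a fixed original. When the original is right on average, pooled O/E points to the update in 83–96% of runs, although the update is better by hospital in about a quarter. When the original is wrong on average, part of the gain is real, but pooled O/E cannot attribute it to the new predictors.

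These sizes rest on assumed hospital differences, equal case mix, log-scale pooling and, in the random-shift runs, an update that adds no predictor information. The point bears on one measure within a primary objective. It does not invalidate the cross-validation or the other measures, and no stated decision rule depends on it.

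**What to change.** For the updated model, and for any recalibrated model assessed in the same way:
- Report the three held-out O/E values with intervals, and their spread, at each time point.
- Base the O/E comparison on per-hospital |log O/E| over the same held-out hospitals (for example root-mean-square or maximum), not on the pooled O/E.
- Add as a comparator the original model recalibrated in the same training folds, so that gain from the four additional predictors is separated from gain from re-estimating the baseline.
- Keep random-effects meta-analysis for the C-statistic and calibration slope.
- State that a pooled cross-validated O/E near 1 will not be cited as evidence of calibration.

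This changes analysis wording only and needs no new data. The cost is slightly more analysis work and a less favourable calibration summary for the updated model.
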